### Data collection

2.4.

For data collection, we use a digital platform that sends invitations to participation and unique personalised links via email/SMS, allowing participants to respond in their own time, via smartphone, tablet or computer. Data is safely and reliably combined by the digital platform software, without personal codes or human handling, thereby maximising confidentiality and minimising risk of error. It will be possible for participants to listen to the survey questions and information about the study.

Given that the experimental group is determined by the standardised procedure of the Swedish National Agency for Education who handles the applications for participation in the SCS-TIC programme, it cannot be claimed that the experimental group is randomly selected. Nevertheless, although access to school (socioeconomic and ethnic) data is restricted by current state regulations, we strive to match the schools that contribute to the experimental group with schools of similar student population composition (class sizes, proportion of immigrant students), geographic location (i.e. urban or suburban-located schools), and socioeconomic status (i.e. location of the school) in the control group. Schools in the control group are randomly selected among those who match on the above criteria, based on a draw.

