### Participants and recruitment

2.3.

Participants will be teachers and other professionals in the school context (principals, special teachers, school nurses) working in Swedish schools, from primary school to high school. Participants in the experimental group (*N* = 160) will be recruited from schools who participate in the SCS-TIC training programme. Sixteen (16) training groups consisting of 35 people each participate in the SCS-TIC training programme each semester. Participants will be excluded if they do not complete the programme. An equally large control group (*N* = 160) will be recruited from schools not receiving the SCS-TIC programme. For recruitment, participants in the experimental group will be contacted through collaboration with SCS. Participants in the control group will be invited to the study through e-mail and targeted on social media platforms.

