### Background variables

2.6.

Background variables will include participants’ age, mother language, gender, profession, work experience, ethnicity, and social class.

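### The draw of matched control schools is stated more firmly than the described data access supports, and no check of, or adjustment for, student composition is described

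*Protocol article*

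**What the plan says.** Section 2.4 (Data collection) concedes that the trained group is not randomly selected, because a government agency decides which schools enter the programme. It then offers matching of schools as the response: "although access to school (socioeconomic and ethnic) data is restricted by current state regulations, we strive to match the schools". Three criteria follow:

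- student composition: "schools of similar student population composition (class sizes, proportion of immigrant students";
- geography: "geographic location (i.e. urban or suburban-located schools";
- socioeconomic position: "socioeconomic status (i.e. location of the school) in the control group".

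The section closes with: "Schools in the control group are randomly selected among those who match on the above criteria, based on a draw".

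Three other sections bear on the point. On recruitment, section 2.3 says: "Participants in the control group will be invited to the study through e-mail and targeted on social media platforms". Section 2.6 reads: "Background variables will include participants’ age, mother language, gender, profession, work experience, ethnicity, and social class". Section 2.7 plans independent t-tests of the outcome measures at baseline, followed by mixed models for repeated measures. The characteristics it names as examples for those models are social class, gender and ethnicity, at participant level.

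**The concern.** A random draw among matching schools needs a list of schools already known to match. Section 2.4 describes the matching as an effort made under restricted data access, yet reports the draw as though that list were complete on every criterion. It does not say which criteria could be applied in full.

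The doubt falls on a characteristic tied to who is trained. Under section 1.3, enrolled schools must have newly arrived and immigrant-background children and lie in a socially vulnerable area. Under section 2.1, schools are prioritised partly on how common trauma is likely to be among their pupils. Several measures in section 2.5 concern students with a non-Swedish background or attitudes to immigrants, so composition may plausibly relate to outcome as well. If the control schools differ in composition and nobody looks, a difference in how staff in such schools change over the year could be read as an effect of training.

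**Working it through.** The plan gives no figure on this point, so the check sets the sections side by side.

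**1. Which criteria does the restriction reach?** The restricted data are socioeconomic and ethnic school data (section 2.4).

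| Criterion | Within the restriction as worded? |
|---|---|
| Class size | No |
| Proportion of immigrant students | Yes, this is ethnic data |
| Urban or suburban location | No |
| Socioeconomic status | Avoided: defined by the school's location |

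The conflict is thus concentrated on one of four items. If that item could not be applied, the match would rest on class size and location, since location serves both as geography and as the stand-in for socioeconomic status.

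**2. Is the achieved match checked in the study data as described?** The variables in section 2.6 ("age, mother language, gender, profession, work experience, ethnicity, and social class") all describe the respondent. The baseline tests in section 2.7 compare outcomes, not schools. No school-level covariate is named for the mixed model.

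**3. Do the analysed control participants come from the drawn schools?** Section 2.4 draws schools. Section 2.3 reaches people by e-mail and social media and does not say that only staff of drawn schools are invited or eligible. If others can join, even a well-matched draw need not describe the schools of the staff who respond.

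**4. What bias could remain?** Let *D* be the difference between arms in mean school composition, *b* the slope of outcome level on composition, and *g* the slope of change since T1 on composition.

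- Unadjusted comparison of arms at one timepoint after T1: bias = (*b* + *g*) × *D*.
- Comparison of change from T1: bias = *g* × *D*, because *b* × *D* is present at both times and cancels.

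Section 2.7 names both within-person comparisons and comparisons of the arms at each timepoint. For the change comparison, only *g* × *D* remains. The documents give neither *g* nor *D*, so no value can be computed. School-level items would make *D* estimable and would let the model estimate *g*.

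**The case against.** A reader might infer that the match cannot be carried out at all. The documents do not support this. Restricted access is not absence of access, the wording promises best effort, class size and location are outside the restriction as worded, and socioeconomic status has a stated proxy.

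A reader might also infer that no school-level variable is collected. That is an inference from silence. The list in section 2.6 is short, concerns participants, is not worded as exhaustive, and stands in a condensed article. Drawing schools on criteria presupposes that someone holds values for whichever criteria were used. Data sources, tolerances and balance tables are commonly left to a fuller document, and their absence here is not the finding.

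Nor is matching the only protection. There is a pre-training baseline, the outcomes are compared at T1, and the models compare within persons. Stable differences in level are therefore visible and largely removed from a comparison of change. The article also admits openly that allocation is not random.

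These objections stand, and they narrow the point. They do not remove the step from an effort to match to an unqualified draw, the unstated link between drawn schools and recruited staff, or the fact that the balance check the article does describe covers outcomes only. The limitations in the Discussion admit incomplete randomisation, but not that the matching itself may be partial.

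**Conclusion.** The point holds in a limited form. The draw is described more firmly than the stated data access allows, chiefly for the proportion of immigrant students. As described, the achieved match on that characteristic is neither checked nor adjusted for, and sections 2.3 and 2.4 do not fit together on where control participants come from.

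The residual risk is mainly that staff in schools of different composition change differently over time. Where arms are compared at single timepoints without reference to baseline, differences in level would matter too. A reader may be tempted to express the bias as a share of the planned effect of *d* = .5, but that would need both the imbalance and the slope to be assumed, and nothing in the documents supports particular values. This is an improvement that should be made to a non-randomised comparison. It is not evidence that the comparison is invalid. It rests on the article as the only document at hand; a fuller protocol or analysis plan may already hold part of the answer.

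**What to change.** 1. At T1, in both arms, add a few school-level items: typical class size, share of immigrant or newly arrived students in bands, and school location. Alternatively, put one query to each principal. Record a school code so that values can be summarised by school.
2. Tabulate the achieved match by arm.
3. Include these values, with their interaction with time, as adjustment variables in the mixed model. The interaction is what addresses differential change.
4. In section 2.4, state which criteria are matched from accessible data and which are only checked afterwards, and do not describe schools as matched on data that could not be obtained.
5. Reconcile the draw in section 2.4 with the recruitment route in section 2.3: say whether only staff of drawn schools may join and, if others may, how they are identified and handled.

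The cost is a slightly longer questionnaire or one message per school, a few extra model terms, and some rewording. Staff-reported shares are approximate, so adjustment will be imperfect. The documents do not say whether the restriction also covers estimates given by staff or principals; the investigators should confirm that it does not. The items belong at T1, because values asked for later would be recalled rather than true baseline values.

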### Childhood adversity and school-based trauma-informed care intervention in Sweden

1.3.

Experiences of adversities in childhood are common also in a Swedish context. Among Swedish youth, 15% reported experiences of some form of negative exposure in childhood, and 10% reported two or more types of negative exposure before the age of 12 (Hagborg et al., 2018). In response to the Swedish government’s assignment (U2019/03787/S) to support the quality of education for newly arrived, non-Swedish-speaking children, and acknowledging the need for enhanced trauma knowledge among educational staff (Skolverket, 2023), Save the Children Sweden (SCS) was commissioned by the Swedish National Agency of Education in 2017 to train school personnel in a psychoeducational TIC school programme based on the Three Pillars intervention. Notably, among the conditions of the Swedish National Agency of Education for enrolling schools to the programme are that the school (a) has newly arrived children and children with immigrant background, and (b) is located in a socially vulnerable area.

Evidently, experiences of racism and racial discrimination are relevant in the Swedish setting. Statistics Sweden reports substantial disparities between children with a foreign background and those with a native Swedish background across various crucial aspects of life, including socio-economic status, family dynamics and educational opportunities (SCB, 2020). For example, more than 40% of children (0–17 years) with foreign (i.e. immigrant) background live in areas burdened by socio-economic challenges, compared to 5% of children with Swedish background. A recent report by SCS (Rosenlundh et al., 2021) indicates that every second child has witnessed racism in the school setting, and every fourth child reported to have experienced discrimination and/or harassment. A fifth of all children reported being afraid of being bullied because of their ethnic background. Notably, the children perceived adults as passive, seldom intervening or doing anything to stop racism in school (Rosenlundh et al., 2021). The school environment appears to be a primary setting where racism against children is perpetrated (Rosenlundh et al., 2021). Thus, an ethnic and culturally informed ACEs framework is highly warranted.

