### The trauma informed care (TIC) psychoeducational intervention for schools

2.1.

The SCS psychoeducational TIC school programme (Bath et al., 2021) provides a pedagogical framework for understanding how significant adults create conditions for healing and recovery in children who are exposed to trauma. With an aim of developing teachers’ ability to respond to pupils with a trauma-informed approach, the 5-day programme builds around the themes of safety, connections, and coping (Bath, 2015), and provides education about compassion fatigue and secondary traumatic stress, practical TIC training, and workshops on TIC implementation at an organisational level. TIC-ambassadors continue to work closely with the principal and support the TIC organisational implementation after finished training. For participation in the SCS-TIC programme, school principals must apply to the Swedish National Agency for Education, who then, based on the school’s written application and interviews with the school principal, select (prioritise) based on parameters including implementation capacity and the likely prevalence of trauma in the pupil population.

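### Control schools are matched on pupil mix and location, but not on having applied or on implementation capacity, two factors that decide entry to the trained group

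*Protocol article*

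**What the plan says.** **How a school enters the trained group.** Section 2.1 of the protocol article says that "school principals must apply to the Swedish National Agency for Education". The Agency then uses the written application and interviews with the principal to "select (prioritise) based on parameters including implementation capacity and the likely prevalence of trauma in the pupil population". Section 1.3 adds two enrolment conditions: that the school "has newly arrived children and children with immigrant background, and (b) is located in a socially vulnerable area".

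**How a school enters the control group.** Section 2.3 requires only that it does not receive the programme. Section 2.4 says "we strive to match the schools that contribute to the experimental group with schools of similar student population composition", meaning class sizes and the share of immigrant pupils, and adds urban or suburban setting and "socioeconomic status (i.e. location of the school"). Control schools are then drawn by lot from those that match. The same section notes that state rules restrict access to socioeconomic and ethnic school data.

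**What is recorded and modelled.** The background variables in section 2.6 describe individual staff members. Section 2.7 plans t-tests of the outcomes at baseline and mixed linear models of the repeated measures. The moderators it names are also personal characteristics.

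**The concern.** The control group is what this trial adds to earlier evaluations, which section 1.4 criticises for lacking one. Its value depends on the two sets of schools being comparable in the respects that led some of them to be trained. A school whose principal sought the training, and which the Agency judged able to carry it out, may be on a different course in attitudes, efficacy or burnout whether or not it is trained. If so, part of any difference in change between the groups reflects selection. If these school factors are never recorded, no later analysis can separate the two.

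This is distinct from how individual control participants are invited. It would remain if every control participant came from a correctly drawn school.

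**Working it through.** The article gives no figure on this point, so the check compares two lists and then follows the consequence through the planned model.

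**Step 1. Selection factors against matching variables.**

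| Factor deciding entry | Source | Counterpart in the section 2.4 matching list |
|---|---|---|
| Newly arrived and immigrant-background pupils | 1.3 | Approximate: proportion of immigrant students (newly arrived is the narrower group) |
| Socially vulnerable area | 1.3 | Approximate: socioeconomic status by location |
| Likely trauma prevalence | 2.1 | Weak proxy only, through the two variables above |
| Principal has applied | 2.1 | None |
| Implementation capacity | 2.1 | None |

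Every trained school applied and was selected. A control school may or may not have applied, and no one has assessed its capacity for this purpose. The groups can be expected to differ on the last two rows, although the article cannot show by how much.

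**Step 2. What the planned model removes.** Let S be an unmatched school factor with mean difference ΔS between the groups. Suppose it shifts the outcome level by λ per unit at every time point, and shifts change from baseline by γ per unit.

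- Level part of the difference in change: λΔS at follow-up − λΔS at baseline = 0.
- Trend part: γΔS, which remains.
- Expected difference in change = training effect + γΔS.

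The baseline measurement therefore deals with a stable difference, provided the effect is read as a difference in change. It does not deal with γΔS. Baseline t-tests on the outcomes are uninformative about γ, because two groups can start level and still diverge.

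**Step 3. How sensitive the test is, under assumption.** The article gives neither γ nor ΔS, so the values of b = γΔS below are assumptions. With 160 per group and the 40% loss stated in section 2.7, 160 × 0.6 = 96 remain per group. The standard error of a difference in SD units is √(2/96) = 0.144. With no true effect, a two-sided 5% test rejects with probability 1 − Φ(1.96 − b/0.144) + Φ(−1.96 − b/0.144):

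| Assumed b (SD) | False-positive rate |
|---|---|
| 0 | 0.05 |
| 0.1 | 0.11 |
| 0.2 | 0.28 |
| 0.3 | 0.55 |

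This ignores clustering by school and treats the two groups as losing equal numbers. It shows what a given b would do, not that b takes any of these values.

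**The case against.** **The limitation is disclosed.** Section 2.4 says that the experimental group cannot be called randomly selected, and the Discussion says that full randomisation is not possible. Section 2.1 reports the selection parameters openly. Differing trends are a risk in any non-randomised design. All of this is true. However, neither acknowledgement names application or capacity, and the plan collects nothing that would let a reader judge their influence. The commitment bias named in the Discussion arises from investment in the training, not from prior selection.

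**The matching covers more than it may seem to.** A reader might infer that controls are matched on nothing that decides entry. The article does not support this. Trained schools meet the two conditions of section 1.3, so matching to them on immigrant proportion and location-based socioeconomic status carries both conditions over approximately.

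**Location.** A reader might also think that location is used twice. Urban or suburban setting and the socioeconomic standing of an area are different attributes, and the restriction on school data explains the area proxy. That restriction is not stated to cover application status or capacity.

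**Non-prioritised applicants are not clearly better controls.** They were passed over on parameters that include capacity and likely trauma prevalence. Because the programme runs every semester, they could also enter it during follow-up. Their number is not given. This objection stands, and it limits what should be recommended.

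**Conclusion.** The point holds for two factors: having applied and implementation capacity. Both decide entry to the trained group, neither has a counterpart in the matching, and the variables that the article lists cannot recover them. The damage is limited to differences in trend.

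Two stronger conclusions are tempting and should not be drawn.

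- **That the training effect is likely overstated.** Motivation and capacity may push that way. A heavier trauma burden in the selected schools, which the matching captures only weakly, could push the other way. The direction is unknown.
- **That the bias is a given share of the planning effect.** Assuming a school difference of 0.3 to 0.8 SD and a correlation with change of 0.2 to 0.3 gives 0.3 × 0.2 = 0.06 to 0.8 × 0.3 = 0.24 SD, or 12% to 48% of d = .5. Nothing in the article supports either input, and it does not say whether d is scaled to the SD of scores or of change.

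This is a worthwhile and inexpensive improvement to the design. It does not invalidate the trial.

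**What to change.** 1. **Record the factors.** In section 2.4, add two or three short items to principals in both groups: whether the school has applied or intends to apply, a rating of implementation capacity, and newly arrived intake. Ask them at baseline, because the training includes work on implementation and could alter a later rating.
2. **Use capacity and intake** as matching variables where possible, otherwise as school-level adjustment covariates.
3. **Use application status differently.** Every trained school applied, so this variable does not vary in that group and should not be entered as an ordinary covariate. Use it for a sensitivity comparison of trained schools with applicant control schools only.
4. **Name the limitation.** State in the Discussion that application and implementation capacity are not matched, and that the direction of any resulting bias is unknown.
5. **Optional.** If the Agency can supply non-prioritised applicants, they may be sampled as controls. This should not be a required first choice, for the reasons given under the objection. Any later entry of such a school into the programme should be recorded.

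The cost is a small added burden on principals. A self-rating is an imperfect substitute for the Agency's interview-based assessment, so adjustment will reduce or expose the confounding rather than remove it. The applicant-only comparison may be small.

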### Primary outcome measures

2.5.

Levels of stress and compassion fatigue are measured by the Professional Quality of Life scale (PROQOL 5: Stamm, 2009), which examines the potential impact from helping others who have experienced trauma and adversities. The scale consists of 30 items divided into three subscales (Compassion satisfaction, *α* = .88, Burnout, *α* = .75 and Compassion fatigue, *α* = .81), with high internal consistency (Stamm, 2010).

Teacher self-efficacy in the classroom environment is measured by the Teachers’ Sense of Efficacy Scale (TSES: Klassen et al., 2014), addressing the distinct domains of pupil engagement, instructional practices and classroom management, with high internal consistency (*α* = .86; Klassen et al., 2014).

The Knowledge and Beliefs’ Survey (KBS: Murray, 2014) assesses self-efficacy, tolerance of child misbehaviour and knowledge of trauma-informed care and consists of 33 items and three subscales (Trauma-Informed Parenting, Tolerance of Misbehaviour, and Parenting Efficacy), all with satisfactory internal consistency (Cronbach’s a .75–.83; Murray, 2014; Sullivan et al., 2016). KBS is commonly used for assessment in the foster care setting. Here, we use a subset of 17 items, adapted to apply in the school setting (e.g. *I routinely think about how students with traumatic experiences are physically safe at our school, but might not feel safe*). The 16 items that specifically concerned out-of-home care (e.g. *I feel confident talking with my child about his/her feelings about his/her biological parents*) were removed.

Awareness about intersectional disparities concerning how ACEs affect individuals and the potential traumatic experiences of racism and discrimination is operationalised utilising three different constructs:
Beliefs and attributions of low academic achievement among students with a non-Swedish background are assessed by the Teacher Attributions of Student Academic Achievement Scale, which encompasses 8 items. The scale was developed and validated in a prior school study (Mohammadi & Wolgast, in preparation) and there is evidence of high internal consistency.Beliefs and attributions concerning mental illness among students with a non-Swedish background are assessed by the Teacher Attributions of Student Mental Health Scale, developed for the purpose of the present project. The scale comprises 16 items organised in two subscales: internal (i.e. individual) attributions and external (i.e. situational) attributions related to the higher risk of mental health problems among non-Swedish youth, compared to their Swedish counterparts. The subscales demonstrate high internal consistency (Hamad et al., in preparation).Negative attitudes toward immigrants are measured by the modern Racism Scale, a 9-item measure that assesses covert forms of racist attitudes toward immigrants (as opposed to blatant and traditional forms of racism). The scale was adapted for the Swedish context with high internal consistency (Cronbach’s *α* = .82; Akrami et al., 2000).

